### 7.2. Exclusion Criteria

- Not eligible to receive one or more drugs according to standard MDA criteria;
- Less than 5 years of age (not eligible for ivermectin)\*\*
- Pregnant women (azithromycin only, not eligible for albendazole and ivermectin)
- Lactating women (Only administered azithromycin and albendazole, not eligible for ivermectin);
- History of allergies to the drugs being studied (azithromycin, ivermectin, albendazole)
- Those who refused to be part of the study (will be addressed via the normal MDA schedule if they prefer with initial treatment with IVM/ALB and azithromycin treatment two weeks later)
- Residents who cannot swallow tablets;

*\*\*Note that patients that are not eligible for IVM, will receive azithromycin and albendazole. Patients that receive azithromycin and albendazole will be followed up through the same procedure as the triple drug therapy to try to track any AEs attributed to the two drug combination.*

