Within our standard arm, the study will deduce the average adverse event rate for azithromycin administered alone using information from previous trials, and it will assume an average adverse event rate for azithromycin, ivermectin and albendazole administered together. For azithromycin, there is a wide-range of reported adverse event rates. The aforementioned co-administration trial in Mali assumed an adverse event rate of 8%. A randomized control trial using a single dose of azithromycin which took place in the United States reported adverse events at 17%. A randomized control trial in Ethiopia reported that monitored adverse event rates after Zithromax MDA reported 4.9%-7.0% adverse events in children from 1-9 years old and 17.0% to 18.7% in persons  $\geq 10$  years of age. Meanwhile, Pfizer labeling reports the following: "Side effects that occurred in patients on the single one-gram dosing regimen of Zithromax with a frequency of 1% or greater included diarrhea/loose stools (7%), nausea (5%), abdominal pain (5%), vomiting (2%), dyspepsia (1%) and vaginitis (1%)." For the purposes of this study, we will set the adverse event percentage at 7% for azithromycin distribution. In terms of the adverse even rate during co-administration of all three drugs, adverse events related to IVM and ALB distribution are largely due to the death of microfilariae, particularly after the first round of MDA in a community. Given that this community has received several years of treatment with both drugs, we assume an acceptable increase in adverse events during co-administration will be 1.5% (Delta), or it will be acceptable for 8.5% of our intervention arm to experience an adverse event.

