The study will require a power of 90% and a two-sided 95% confidence interval for the difference between rates. Given that gotes will be randomly selected from within the same woreda, have all had the same number of years of treatment with each drug, and share the same cultural and environmental factors, we will assume a low variability between each cluster. In case there are unforeseen differences between the clusters, we will include a variance between 6-8%. Conservatively assuming that each gote has a population of 190 individuals, the study will require at least 36 gotes in each study arm to reach 13,600. To take non-compliance, etc. into account, the study will randomize the 42 gotes into each study arm to reach 8,000 participants in each arm from the list of gotes in Kofele woreda into the control and study arms until each arm has 8,000 participants (to account for non-compliance, etc.). Gotes will be chosen via the RANDNUM function in excel. The randomization itself will be conducted via public randomization ceremonies.

Table 2: Assumption Summary

|                                                               |                                                           |
|---------------------------------------------------------------|-----------------------------------------------------------|
| Adverse event prevalence                                      | 7% on average                                             |
| Acceptable adverse event percentage during co-administration: | 8.5%                                                      |
| Delta                                                         | 1.5%                                                      |
| Variance                                                      | Adverse event prevalence between clusters will be 6-8%    |
| Power                                                         | 90%                                                       |
| CI                                                            | 95%                                                       |
| Minimal Number of Gotes Required for each arm                 | 36                                                        |
| Population per cluster                                        | 190 individuals per cluster (gote) on average             |
| Total Population of Study                                     | 13,600 (Rounded to 16,000 for refusals/loss to follow up) |

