After getting the collective informed consent of the community, the HEWs will update the MDA register with the population and household information within the community as per the usual pre-MDA registration activities. While going house to house, the HEWs will read the study consent form to all members of the household and gain their verbal permission to participate in

the study. For those participants that refuse consent, they will be allowed to receive MDA treatment via the usual MDA schedule of IVM/ALB dose followed by azithromycin dose two weeks later.

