## 8.8 Co-Administration Schedule

*The study will have two cohorts control arm, which will receive the usual MDA, and study arm which will receive the triple co-administration. Each arm will have approximately 6,800 people, 42 Gotes. Primarily, the clustering will be made by geography where 42 adjacent Gotes will be in one and the other 42, in another. Which cluster will be the control or study arm will be decided by simple lottery method.*

*After decision on the study arms, the study team will conduct the training and the actual co-administration for a 17-day period (three days for training and 14 days for actual co-administration and surveillance). In total, the entire study will take 45 days to complete.*

**On Day 1**, after the three-day co-administration training module described above, 60 households (HH) or roughly 300 people will be targeted for MDA subjects included in the study will receive concomitantly azithromycin (up to 1 g or four 250 mg tablets), ivermectin (up to 12 mg or four 3 mg tablets) and albendazole (one 400 mg tablet per included subject irrespective of height and age). This will mean that the four teams in the trial arm and the four teams in the control arm will have treated 1200 people each (300 x 4) by the end of Day 1. Teams will remain at the location of the MDA for the entire day and night on standby in case there are any immediate complaints from the targeted beneficiaries. Note that, as described in the “Intensified medical access precautions” section, a medical doctor will remain centrally located between within the woreda throughout the 14 actual days of distribution in the unlikely occurrence of a reaction to the medication.

**On Day 2**, the clinical nurses on each team, led by the three HDA members, will travel to all 60 households within their team’s catchment area to confirm that all 300 persons that received drugs on Day 1 are all healthy and to document any AEs/SAEs that may have occurred. This will also serve as opportunity for a person-to-person coverage survey for later analysis. At the end of the day, the four teams from each arm, together with the independent monitors, PI, supervisors, etc. will meet and discuss if there were any results that should cause concern. While the clinical nurses conduct the house-to-house visits, the HEWs on each team will move to the next group of 60 households targeted for the Day 3 MDA and mobilize that community.

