### 8.9 Data Collection and Statistical Analysis

Data about individual participant will be collected by the study team using structured questionnaires and coded, de-identified labels which will be held in strict confidence. All results will be presented in a way that does not allow individuals to be identified. No information concerning the study or the data will be released to any unauthorized third party. These questionnaires are presented in the appendix of this protocol. The study team will rely on electronic data capture and will convert these forms to the ODK electronic format at the London School of Hygiene and Tropical Medicine.

Table 4: Data Collection Summary for AE reporting

| Forms                                                                                  | Timeline                                                                                                           | Person responsible for filling out the form |
|----------------------------------------------------------------------------------------|--------------------------------------------------------------------------------------------------------------------|---------------------------------------------|
| Informed Consent                                                                       | Pre-MDA Census days and Distribution Day                                                                           | HEW/Clinical Nurses                         |
| Socio-demographic/health Information                                                   | Distribution Day                                                                                                   | Clinical Nurses                             |
| Study drug registry                                                                    | Distribution Day                                                                                                   | Clinical Nurses                             |
| Contra-indication/AEs reporting to the Co-Administration team (HEW and clinical nurse) | Day 2, Day 4, Day 6, Day 8, Day 10, Day 12, Day 14, Day 17+18 follow up or at any time during passive surveillance | Clinical Nurses/HEW                         |
| Contra-indication/AEs reporting to the local health post (HEW)                         | Day 19-30                                                                                                          | HEW                                         |

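### Individual consent appears to follow the arm decision and refusers leave the study for the control regimen, so who enrols can differ by arm in a comparison with a 1.5-point margin

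*Protocol*

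**What the plan says.** **Arm decision.** Section 8.1 has gotes allocated at public ceremonies. Section 8.8 has two blocks of 42 adjacent gotes assigned by a simple lottery. It continues: "After decision on the study arms, the study team will conduct the training and the actual co-administration for a 17-day period", with three days of training and then 14 days of distribution and surveillance.

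**Consent.** Section 8.2 runs from training to mobilization, then collective community consent, then the register update with individual consent: "While going house to house, the HEWs will read the study consent form to all members of the household". Table 4 in section 8.9 gives the timing of informed consent as "Pre-MDA Census days and Distribution Day". In section 8.6.2 the nurses confirm assent before the drugs are given.

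**Refusal.** Section 7.2 lists as excluded: "Those who refused to be part of the study (will be addressed via the normal MDA schedule if they prefer", with ivermectin/albendazole first and azithromycin two weeks later. Section 8.2 repeats this. It is the regimen that the Study Protocol Summary gives to the control arm.

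**Enrolment and analysis.** The Study Protocol Summary continues enrolment until the sample size is reached. Section 8.9 names severity and treatment package as the covariates of the clustered logistic regression.

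**The concern.** Cluster randomization balances the people living in the gotes. It does not balance the people who agree to take part once their arm is known. A trial-arm resident who is wary of taking everything at once can decline and receive the familiar schedule; a control-arm resident who declines gets the same drugs as before. Section 11 recognises that up to nine pills at one time may cause physical and mental duress, so a reason to decline that is specific to the trial arm is foreseeable.

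If willingness to enrol is related to the risk of having or reporting an adverse event, the arms are no longer comparable. The primary outcome rests on reported adverse events and the margin is 1.5 points, so a modest difference in who enrols matters. Filling each arm to its target number can also hide unequal refusal.

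**Working it through.** **1. Order of events.** Section 8.8 places the arm decision before training. Section 8.2 places training before mobilization, community consent and household consent. Table 4 allows consent on distribution day, which necessarily follows the arm decision. Nothing in the protocol provides for individual consent before allocation or for recruiters unaware of the arm. The order comes from reading these sections together; the section 8.8 sentence does not itself mention consent.

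**2. The design figure.** Section 8.1: "The study will require a power of 90% and a two-sided 95% confidence interval for the difference between rates"; a rate of 7% ("we will set the adverse event percentage at 7% for azithromycin distribution"); margin 1.5 points; 190 people per gote; and "we will include a variance between 6-8" percent, read here as ±2 SD, so a between-gote SD of 0.5 point (an assumption).

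c = 1 + (1.960 + 1.282)² × [2 × 0.07 × 0.93/190 + 2 × 0.005²] / 0.015² = 35.34, rounded up to 36 gotes; 36 × 190 = 6,840 per arm.

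This matches sections 6 and 8.1. At 7% in both arms the standard error of the difference is √{[2 × 0.07 × 0.93/190 + 2 × 0.005²]/36} = 0.45 point. Moving consent before the draw changes none of these inputs.

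**3. Sensitivity to selective refusal.** Let q be the share refusing, in the trial arm only, and RR the refusers' risk relative to those enrolled. If the whole eligible population has a rate of 7%, the enrolled rate is 7% / (1 − q + q × RR). The protocol gives neither q nor RR, so both are assumptions.

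| q | RR | Observed trial-arm rate | Change (points) |
|---|---|---|---|
| 5% | 2 | 7/1.05 = 6.67% | −0.33 |
| 10% | 2 | 7/1.10 = 6.36% | −0.64 |
| 15% | 2 | 7/1.15 = 6.09% | −0.91 |
| 10% | 3 | 7/1.20 = 5.83% | −1.17 |
| 10% | 0.5 | 7/0.95 = 7.37% | +0.37 |

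The last row shows that the sign depends on who refuses. If refusal were 10% with RR 2 in both arms, both would read 6.36% and the difference would be unaffected. For scale, section 6 allows a cushion it calls 15% (13,680 of 16,000 leaves 14.5%), but that covers non-compliance and exclusions generally, not refusal alone.

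**4. What a shift does to the test.** If the true difference is exactly 1.5 points (7% v 8.5%), the standard error is √{[0.07 × 0.93/190 + 0.085 × 0.915/190 + 2 × 0.005²]/36} = 0.47 point. With a downward shift b, the chance of wrongly concluding non-inferiority is Φ(b/0.47 − 1.96): 2.5% at b = 0, about 7.6% at b = 0.25 point and about 18% at b = 0.5 point. With a between-gote SD of 1 point the last two are 7.0% and 16%. An upward shift would instead cost power.

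**5. Age as one route.** Section 8.1 cites azithromycin rates of 4.9–7.0% at ages 1–9 and 17.0–18.7% at 10 and over, a gap of 10.0 to 13.8 points. A 5-point difference between arms in the share aged 10 and over moves the comparison by 0.05 × 10.0 = 0.5 to 0.05 × 13.8 = 0.7 point, in either direction.

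**The case against.** **Certainty of the order.** No sentence dates household consent against the draw. Table 4 does not date the census days, and the 17 days in section 8.8 include none for a census. This stands: the order is an inference from several sections, though they agree and none contradicts it. Section 8.6.2 can also be read as mere confirmation on distribution day, but Table 4 lists consent itself for that day.

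**Incentives.** A reader might infer that the incentive to refuse exists only in the trial arm. The protocol does not support that. Control residents who refuse avoid questionnaires and house visits, which section 8.8 runs twice in that arm. Trial-arm refusers give up the saving in time that section 11 expects beneficiaries may value. Someone with an earlier reaction may refuse in either arm. The incentives are unequal, not one-sided.

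**Direction.** A reader might also infer that the trial-arm rate will be lowered and non-inferiority favoured. That cannot be established. Control participants who do not return for azithromycin, for example, would lower the control rate and work against non-inferiority.

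**Safeguards.** The protocol has a household register, a recruitment form with symptoms and consent status, a coverage survey, independent monitors, age-stratified adverse event reporting, and DSMB review of recruitment and losses. These may reveal a difference but do not prevent one. Table 4 collects health information on distribution day, so people who refuse at the household would have no baseline symptoms on record.

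**Common practice.** Consent after allocation is usual in open cluster trials, and reporting of refusals can be left to the SAP. Both are fair. The SAP cannot recover data never collected on refusers, however, and here this order meets a narrow margin and exclusion of refusers.

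**Conclusion.** The concern holds as a design weakness, not as a demonstrated bias. Read together, sections 7.2, 8.1, 8.2, 8.6.2, 8.8 and 8.9 put the arm decision before individual consent and remove refusers, who then receive the control regimen. Enrolment can therefore differ by arm, and nothing stated prevents it. The direction and size are unknown.

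The illustrative range is a fall of 0.33 to 0.91 point in the observed trial-arm rate. It rests wholly on assumptions: a true rate of 7%, 5% to 15% refusal in the trial arm only, and refusers at twice the risk. It shows that plausible selection could be a material part of the 1.5-point margin, not that it will be. The planned 36 gotes per arm are not in question on this point.

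**What to change.** 1. List the 84 gotes first. Section 8.8 already defines two blocks before the lottery; section 8.1, which allocates gotes until each arm reaches 8,000, needs the list fixed in advance.
2. Complete the census register and individual consent in all 84 gotes with one arm-neutral script describing both regimens. Hold the draw only after that, and say so in sections 8.1, 8.2, 8.8 and Table 4.
3. On distribution day, only confirm willingness and recheck eligibility.
4. Collect age, sex and baseline symptoms at the census, so that people who withdraw after the draw can be counted and compared by arm.
5. Keep the treated-and-followed population for the main safety comparison and add a sensitivity analysis for withdrawals after the draw. Making everyone consented before the draw the main population would require new follow-up of later refusers. It would also dilute a true excess: if 10% of the trial arm took the control regimen, a 1.5-point excess would shrink to 0.9 × 1.5 = 1.35 points.

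Cost: a short gap between consent and dosing, a longer consent script, baseline items moved to the census, and an eligibility recheck. The sample size is unchanged. This is a cheap improvement.

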**On Day 17, 18**, the clinical nurses and HEW from each of the original four teams will perform one last house to house follow up of all the households that received the triple drug administration. (400 HH x 4 teams = 1600 HH) This will be the last active follow-up step.

**Day 19-30**, the HEWs will maintain the reporting form for another two weeks in the event of any additional complaints from the targeted beneficiaries. This will be completely passive and the HEW will only log complaints if they are reported by a beneficiary. On Day 30, all of the co-administration registers and forms will be collected for data analysis from the HEWs.

Note that in the “standard MDA” control arm, the process described above will be conducted twice. First, IVM/ALB MDA will take place for with 14 days of active surveillance then the Trachoma MDA will take place for 14 days of active surveillance. Passive surveillance will continue in the control arm for two weeks after that.

Once the 45th day of the study is reached in Oromia, the field implementation portion of the study will be complete. The DSMB will review the final data before making a recommendation on how the remainder of the population in the woreda should be treated. Should the DSMB and the FMOH agree, the remaining 4-5000 beneficiaries within Homesha will be targeted for co-administration. However, at this juncture, the RCT will be over. The study will move to strictly observational with the same enhanced supervision in place.

Table 3: Follow up Schedule for both the Trial and the Control Arms of the Study

|                                                    | Day 1 | Day 2 | Day 3 | Day 4 | Day 5 | Day 6 | Day 7 | Day 8 | Day 9 | Day 10 | Day 11 | Day 12 | Day 13 | Day 14 | Day 15 | Day 16 | Day 17 | Day 18 | Day 19-30 | Day 31 |
|----------------------------------------------------|-------|-------|-------|-------|-------|-------|-------|-------|-------|--------|--------|--------|--------|--------|--------|--------|--------|--------|-----------|--------|
| Actual Distribution                                |       |       |       |       |       |       |       |       |       |        |        |        |        |        |        |        |        |        |           |        |

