| Next Day Follow-up                                 |       |       |       |       |       |       |       |       |       |        |        |        |        |        |        |        |        |        |           |        |
| One week follow up                                 |       |       |       |       |       |       |       |       |       |        |        |        |        |        |        |        |        |        |           |        |
| 14 Day Follow up                                   |       |       |       |       |       |       |       |       |       |        |        |        |        |        |        |        |        |        |           |        |
| Passive Surveillance                               |       |       |       |       |       |       |       |       |       |        |        |        |        |        |        |        |        |        |           |        |
| DSMB Review (or as needed via charter description) |       |       |       |       |       |       |       |       |       |        |        |        |        |        |        |        |        |        |           |        |

Figure 1: Randomization and MDA distribution Plan in Trial and Control arms

[figure not shown]

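### Section 8.8 gives conflicting rules on whether the control arm has a last house-to-house adverse event visit after its azithromycin dose

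*Protocol*

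**What the plan says.** Section 8.8 of the protocol sets out the schedule day by day. Each team treats on the odd days from Day 1 to Day 13, and nurses visit the treated households on the following day, so next-day visits end on Day 14. Days 15-16 are self-report only. On Days 17-18 nurses and extension workers "perform one last house to house follow up of all the households that received the triple drug administration". The text counts this as 400 households for each of four teams, 1,600 in all, and adds: "This will be the last active follow-up step". Days 19-30 are passive.

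The control arm is then covered in three sentences. In the "control arm, the process described above will be conducted twice". Next: "First, IVM/ALB MDA will take place for with 14 days of active surveillance then the Trachoma MDA will take place for 14 days", the second block being active too. Then: "Passive surveillance will continue in the control arm for two weeks after that".

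Other places bear on this:

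- The title of Table 3 is "Follow up Schedule for both the Trial and the Control Arms of the Study". Its rows include "One week follow up" and a two-week follow-up, but the marks in its cells did not survive and Figure 1 is not shown.
- Table 4 in Section 8.9 lists the Day 17+18 follow-up without naming an arm.
- Section 8.7 describes next-day follow-up only for people given the triple drug.
- Section 8.5 and the DSMB charter place the concluding comparison on Day 31, while the end of Section 8.8 has the board review the final data once Day 45 is reached.

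**The concern.** The primary outcome is the incidence of adverse events over about a month, compared between arms against a margin of 1.5 percentage points (Section 8.9). House visits are a main route by which mild and moderate events come to light. If one arm has a late house visit after its final dose and the other does not, events are sought differently by arm, and the comparison mixes drug effect with search effort. No later analysis can recover visits that were not made, so the protocol has to settle the calendar. In the readable text it gives two rules that cannot both be followed, and teams could resolve the conflict in different ways.

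**Working it through.** No sample-size formula bears on this point; the check is a count of days and visits from Section 8.8. Day 1 is the first dosing day.

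**Trial arm.** Dosing is on Days 1, 3, ..., 13, with a next-day visit and a last visit on Day 17 or 18.
- Shortest gap from dose to last visit: 17 - 13 = 4 days.
- Longest gap: 18 - 1 = 17 days.

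**Whose households are counted on Days 17-18.** The schedule uses 60 households for 300 people, or 5 per household. Then 1,600 x 5 = 8,000 people, which is one arm. The count agrees with the triple-drug wording, although the section often counts per arm.

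**Control arm, rule A (whole process repeated).** The Study Protocol Summary puts azithromycin two weeks after ivermectin/albendazole, so every second-round date shifts by 14.
- Azithromycin dosing: Days 15, 17, ..., 27. Next-day visits: Days 16 to 28. Last visit: Days 31-32.
- Gap from final dose to last visit: 31 - 27 = 4 to 32 - 15 = 17 days, as in the trial arm.
- Repeating the first-round Days 15-18 block as well would put it on azithromycin Days 1-4. On Days 17-18 each control team would owe about 400 last visits on top of a 300-person session and 60 next-day household visits. That part of the repeat is not workable.

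**Control arm, rule B (fourteen active days per round, then passive).** Days 1-14 of a round contain only the next-day visit. The last active contact is therefore 1 day after the azithromycin dose.

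**Does the stated 45-day total decide between them?** It does not.
- With training and no late control visit: 3 + 14 + 14 + 14 = 45.
- Without training, the Day 31 schedule shifted by two weeks, late visit included: 14 + 31 = 45.

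**Does control lose active contact after ivermectin/albendazole?** It does not. A household dosed on Day 1 is seen at the azithromycin next-day visit on Day 16, and 16 - 1 = 15 days. The gap concerns azithromycin only.

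| | Last active visit after the final dose |
|---|---|
| Trial arm | 4-17 days |
| Control, rule A | 4-17 days |
| Control, rule B | 1 day |

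**The case against.** The strongest reply is that the governing sentence is the one that repeats the whole process, that this process contains Days 17-18, and that the Table 3 title and Table 4 set no arm limit. The fourteen-day sentences may only give the order of the rounds: Section 8.8 also uses fourteen days as shorthand for the trial arm's block, which Days 17-18 still follow. The triple-drug wording may be loose, since Section 8.7 uses it for next-day visits and the event form in Appendix 4 asks every respondent about three drugs. On that view a late control visit was always meant. This may be so, but no readable sentence gives its date, and the text goes straight from fourteen active days to passive surveillance.

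A second reply is that events are captured in other ways: return trips to treated communities, volunteers who stay in each gote, and collection at health posts after a month. None of these is limited to one arm, and they soften the gap. They are not house visits and do not replace one.

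Two stronger readings are tempting and should be resisted. A reader might set four control visits against two. The four-visit schedule cannot be staffed, so it is not a real alternative; the open question is the single visit after azithromycin. A reader might also say flatly that the protocol never dates such a visit. With the Table 3 marks and Figure 1 unreadable, that cannot be claimed.

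**Conclusion.** The concern holds as a conflict in the readable text of Section 8.8 over one visit: the last house visit in the control arm after azithromycin. If the fourteen-day wording is followed, active case finding ends 1 day after the final dose in control, against 4-17 days in the trial arm. This assumes rounds two weeks apart and dosing on alternate days, as written, and it falls away if Table 3 or Figure 1 already shows a matched visit, although the prose would still need correcting.

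A reader might infer that the result would be biased in a known direction. The document does not support that. On the fourteen-day reading the trial arm has a late visit that control lacks, while control has a second next-day visit that the trial arm lacks. The two pull in opposite directions, and the protocol gives no yield per visit. Unequal ascertainment is established for that reading; its effect on the 1.5-point comparison is not.

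**What to change.** Write out one control calendar in Section 8.8, with Day 1 as the first dosing day:

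- Ivermectin/albendazole on Days 1-14 and azithromycin on Days 15-28, with no separate first-round block on Days 15-18.
- The same last house visit after the final dose in both arms: trial Days 17-18, control Days 31-32.
- Wording in Sections 8.7 and 8.8 that covers both arms in place of the triple-drug phrase, and a fourteen-day sentence that agrees with the calendar.
- A statement of whether the 45 days run from training or from first dosing. The control visit fits either way: Days 31-32, or study days 34-35 if three training days are counted. Passive surveillance shifted by two weeks ends on 30 + 14 = Day 44, which fits if the count starts at first dosing; with training it would be study day 47.
- The same shift for control forms. At present "On Day 30, all of the co-administration registers and forms will be collected for data analysis from the HEWs", which on a single study calendar precedes the control visit.
- The final DSMB comparison after control follow-up ends, on Day 45 as the end of Section 8.8 already implies, with Section 8.5 and the charter changed from Day 31.

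The cost is a wording and calendar amendment and two days of visits by the existing control teams, about 400 households each, the load already planned for the trial teams. Control keeps one extra next-day visit because it has two dosing days; that difference remains and should be acknowledged.
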